### Compliance assessment and safety assessment

3.7

Participants’ compliance will be assessed at the end of week 4. Participants with scores of less than 80 will be considered to have poor compliance.

$$\mathrm{Compliance}\;\mathrm{score}=\frac{\mathrm{Number}\;\mathrm{of}\;\mathrm{actual}\;\mathrm{treatment}\;\mathrm{sessions}}{\mathrm{Number}\;\mathrm{of}\;\mathrm{required}\;\mathrm{treatment}\;\mathrm{sessions}}\times 100\%$$

Participants will be instructed to report adverse events during the study period. Common adverse events associated with acupuncture include dizziness, paresthesia, needle-site bleeding and pain, etc. All adverse events will be recorded and assessed by the researchers in detail, including symptoms, occurrence time, duration, severity, management, resolution, and causality relationship with the intervention (41, 42).

### Sample size

3.8

This trial will compare the two EA waveforms in different BP severity groups. However, studies with comparable designs are lacking. According to a study by Sim and Lewis (43, 44), a pilot trial of at least 55 participants would minimize the overall sample size for small to medium standardized effect sizes. Therefore, we will recruit 120 participants in total, with 60 participants at each severity level. And participants will be assigned to the two treatment groups in a 1:1 ratio.

### Statistical analysis

3.9

Statistical analysis will be performed using SAS software version 9.3 (SAS Institute Inc., United States). Numerical data with normal distribution will be presented as mean ± standard deviation, whereas non-normally distributed data will be shown as median and interquartile range. For categorical data, the frequency and percentage of each category will be presented. The Student’s *t* test or Mann–Whitney U test will be used for comparisons of numerical variables, and the chi-squared test or Fisher’s exact test will be used for comparisons of categorical variables. All statistical tests will be two-sided, with the significance level set at 0.05. Both intention-to-treat and per-protocol populations will be analyzed. Missing data will be substituted using the last observation carried forward method. After the primary statistical analysis, a power analysis will be conducted using G*Power software version 3.1.9.7 (Heinrich Heine University Düsseldorf, Germany) to evaluate the statistical power of the study given the sample sizes and the obtained effect sizes.

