### Randomization and allocation concealment

3.3

In total, 120 participants are planned to be enrolled from three clinical centers. Based on the patient volume and available resources at each center, we plan to recruit 70 participants from the First Affiliated Hospital of Zhejiang Chinese Medical University, 30 participants from the Third Affiliated Hospital of Zhejiang Chinese Medical University, and 20 participants from Hangzhou First People’s Hospital. For both severity levels, participants in all three clinical centers will be randomly assigned in a 1:1 ratio to the low frequency continuous wave group or the intermittent wave group using the same central computer system (DAP Software Co., Ltd., China) by an independent researcher at each clinical center. Allocation to treatment groups will be under the control of this system automatically, and therefore, will not be influenced by either researchers or participants.

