#### Primary outcome

3.6.1

*Change from baseline score of the Facial Nerve Grading System 2.0 at week 4.* The Facial Nerve Grading System 2.0 (FNGS 2.0) is an update version of the original House-Brackmann (H-B) scale (37). A study have shown that the inter-rater consistency when using the H-B scale is significantly influenced by the experience level of the assessors. In contrast, the FNGS 2.0 demonstrated better repeatability and consistency, independent of the assessor’s experience, indicating improved accuracy (38). Therefore, this pilot trial, we will use the FNGS 2.0 instead of the original H-B scale. In the FNGS 2.0, function of four facial regions including brow, eye, nasolabial fold, and oral commissure, and the global impression of secondary movement are separately assessed. Therefore, confusion can be addressed when different regions do not conform to a certain grade on the original H-B scale. Each area is assigned a score of 1–6, and the severity of secondary movement is assigned a score of 0–3, with higher score indicating poorer function. The final score is determined by combining the four regional and secondary movement scores. The primary outcome of this trial will be the change from baseline score of FNGS 2.0 at week 4.

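### The primary change in FNGS 2.0 is compared by an unadjusted two-sample test that makes no use of baseline FNGS 2.0; the test is valid on average but gives up precision, by an amount that may be small

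*Protocol article*

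**What the plan says.** Section 3.6.1 of the protocol article fixes the endpoint: "The primary outcome of this trial will be the change from baseline score of FNGS 2.0 at week 4". It also defines the scale: "Each area is assigned a score of 1–6, and the severity of secondary movement is assigned a score of 0–3", summed over four facial regions plus secondary movement. Section 3.2 requires an entry score of at least 15 and excludes synkinesis; the Discussion gives the entry range as 15 to 24.

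Section 3.9 names the analysis. For numerical variables, the Student's t "test or Mann–Whitney U test will be used for comparisons of numerical variables". It adds: "All statistical tests will be two-sided, with the significance level set at 0.05". No covariate, regression model or stratified test appears in the article.

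On size, section 3.8 says "we will recruit 120 participants in total, with 60 participants at each severity level", split 1:1 between waveforms. This rests on a cited rule that "a pilot trial of at least 55 participants would minimize the overall sample size for small to medium standardized effect sizes", because "studies with comparable designs are lacking". No target difference, SD, baseline-to-week-4 correlation or planned power is given. Section 3.3 randomises 1:1 at both severity levels across three centres planned at 70, 30 and 20 patients; it does not say that randomisation is stratified by centre.

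**The concern.** A change score is not free of its starting value. On this scale, two patients who reach the same final state record different changes if they entered at different scores, so an arm that happens to start worse can appear to improve more. A two-sample test on changes has no means of separating that from a waveform effect.

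At stake is the precision of a small trial and the credibility of its estimate if the arms differ at baseline. The trial is a pilot meant to inform later research, so an adjusted mean difference with its confidence interval is worth more than a bare p-value. A Mann–Whitney result would not supply a mean difference at all, and section 3.9 gives no rule for choosing between the two tests beyond tying the summary statistics to normality.

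**Working it through.** **The plan's own figures.** 2 × 60 = 120 and 70 + 30 + 20 = 120, so the totals agree. At 1:1 there are 30 per arm in each severity level. No power formula can reproduce the 120, since no effect size, SD or power is stated.

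**Dependence of change on baseline.** The scale minimum is 4 × 1 + 0 = 4. Four regions at 6 with no secondary movement give 4 × 6 = 24, which matches the stated entry range. The largest possible improvement is 15 − 4 = 11 points from an entry score of 15, and 24 − 4 = 20 points from 24.

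**Assumptions (not in the article).** Baseline SD (SDb) 2 to 3 points, week-4 SD (SDf) 3 to 5 points, correlation (ρ) 0.2 to 0.6.

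**Chance imbalance within a severity level.** The standard error of the baseline difference between arms is SDb × √(2/30):
- SDb = 2: 2 × 0.258 = 0.52 points
- SDb = 3: 3 × 0.258 = 0.77 points

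If the levels were pooled (60 per arm), the factor is √(2/60) = 0.183, giving 0.37 to 0.55 points.

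**How much of it reaches the estimate.** Let the slope of week-4 score on baseline be β = ρ × SDf / SDb. A baseline difference D shifts the expected difference in improvement by (1 − β) × D. At mid-range (SDb 2.5, SDf 4, ρ 0.4), β = 0.4 × 4 / 2.5 = 0.64. A two-standard-error imbalance is 2 × 2.5 × 0.258 = 1.29 points, so the shift is 0.36 × 1.29 = 0.46 points. With β = 0.4, the same two-standard-error imbalance (1.0 to 1.5 points for SDb 2 to 3) shifts it by 0.6 to 0.9 points. With β = 1 the shift is zero.

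**Precision.**
- Variance of change = SDb² + SDf² − 2ρ·SDb·SDf
- ANCOVA residual variance = SDf²(1 − ρ²)
- The first equals the second plus (1 − β)² × SDb²

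| SDb | SDf | ρ | β | Variance of change | ANCOVA variance | Ratio |
|---|---|---|---|---|---|---|
| 3 | 3 | 0.2 | 0.20 | 14.40 | 8.64 | 0.60 |
| 3 | 3 | 0.6 | 0.60 | 7.20 | 5.76 | 0.80 |
| 2.5 | 4 | 0.4 | 0.64 | 14.25 | 13.44 | 0.94 |
| 2 | 4 | 0.5 | 1.00 | 12.00 | 12.00 | 1.00 |

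Over an even grid of the assumed ranges, the ratio runs from 0.60 to 1.00 with a median of 0.94. About two thirds of the grid gives a variance reduction below 10%, and about 4% gives more than 25%. The 0.60 is reached only at the corner in the first row. At mid-range, the standard error of the waveform difference in one level falls from √(14.25 × 2/30) = 0.97 to √(13.44 × 2/30) = 0.95 points.

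**Validity of the unadjusted test.** In a simulation with 30 per arm (baseline uniform on 15 to 24, week-4 scores bounded below by 4, no waveform effect, 20,000 trials), the unadjusted t test rejected in 5.0% of trials and the variance ratio was 0.83. The distributions are assumed.

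**The case against.** The strongest reply is that little is lost. The trial is a pilot without a power target, so no stated power is missed. At mid-range the variance reduction is about 6%, and a two-standard-error imbalance, which is itself uncommon, moves the estimate by roughly half a standard error (0.46 against 0.97). The 11-versus-20 contrast assumes full recovery by week 4, whereas patients are selected for slow recovery, and the Introduction cites at least four months for ENoG below 20%. All of this stands. It limits the size of the point, not its direction: within the assumed ranges, the large-sample variance of ANCOVA is never the larger.

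It can also be said that covariate lists belong in an analysis plan that is not shown. That holds for centre terms and choice of standard error. It does not fully answer the main point, because section 3.9 positively names the two-sample tests for numerical variables and the primary outcome is one of them.

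Three stronger readings are not supported by the article:
- A reader might infer that the test is biased or has an inflated error rate. Randomisation prevents this on average; the exposure is to whatever imbalance happens to occur.
- A reader might infer that the ENoG information is thrown away. The 20% cut defines recruitment, randomisation and the comparison by severity. Only variation within a level is unused, although section 3.9 does not itself say whether the test is run by level or pooled.
- A reader might infer that the analysis must adjust for centre. Stratification by centre is not stated, so this is desirable with centres of 70, 30 and 20, but not shown to be required by the randomisation.

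**Conclusion.** The point holds as one of efficiency and robustness. The article commits the primary change score to an unadjusted comparison, although the attainable change depends on an entry score that is already collected. The price is a variance between equal to and 1.67 times that of ANCOVA (1/0.60), and about 1.06 times at mid-range (1/0.943). In addition, chance baseline differences with a standard error of 0.52 to 0.77 points pass in part into the estimate. These figures rest wholly on assumed SDs and correlations and on analysis within each severity level. Where the slope is near 1, which may be so in the ENoG-below-20% level if few patients approach the floor in four weeks, there is almost nothing to gain. The change is worth making because it is nearly free, not because the present test is invalid.

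**What to change.** In section 3.9, or in the analysis plan before unblinding, name the primary analysis as an ANCOVA of week-4 FNGS 2.0 (or, equivalently for the waveform effect, its change) on waveform and baseline FNGS 2.0. Fit it within each ENoG level, or pool the levels with severity and waveform-by-severity terms and report the effect at each level. A pooled model with severity only as a main effect would not do: it yields one common waveform effect, whereas the stated aim is to compare the waveforms in the different severity groups.

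Report the adjusted mean difference with its 95% confidence interval. Use the same approach for the Sunnybrook scores and the CMAP amplitude, each with its own baseline. Keep the rank test as a prespecified sensitivity analysis. Centre and continuous ENoG are optional further covariates.

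The cost is wording, since the covariates are already collected, and a few degrees of freedom. Within a level of 60, adding baseline alone takes the residual degrees of freedom from 60 − 2 = 58 to 60 − 3 = 57; centre would take two more. Where the slope is close to 1, that small cost brings no gain in return.

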## Introduction

1

Bell palsy (BP), also known as idiopathic facial paralysis, is a neurological condition that affects facial nerve function with unclear pathogenesis (1). BP is the most common cause of acute facial palsy, accounting for approximately 75% of all cases (2, 3). The reported annual incidence of BP ranges from 11.5 to 53.3 per 100,000 persons in different populations (4, 5). Functional and esthetic impairments are common among individuals with BP, as the most prominent symptom of the condition is the sudden weakness of facial muscles, which usually reaches peak severity within 72 h, leading to a drooping eyelid and corner of the mouth and even the complete loss of facial movement (6). And other symptoms may include decreased taste, hyperacusis, and pain around the ear or jaw (7, 8). In addition, patients with BP may face a heightened risk of psychological disorders, including anxiety and depression, and may also experience a decrease in overall quality of life (9).

Bell palsy has a generally fair prognosis, with most patients experiencing important improvement within 3 weeks (10). Even without intervention, approximately 70% of patients achieve complete recovery within 6 months (2). However, permanent paresis or paralysis occurs in a minority of the patients. The use of electroneurography (ENoG) to objectively measure the severity of facial nerve damage can aid in predicting prognosis (11–13). In ENoG testing, surface electrodes record the compound muscle action potential (CMAP) of facial muscles following electrical stimulation to the main trunk of the facial nerve. The ENoG value is calculated as the ratio of the CMAP amplitude on the impaired side to that on the normal side (14). A previous study showed that an ENoG value of less than 20% predicted a recovery period of at least 4 months, with the possibility of incomplete recovery in the worst cases (15).

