#### Secondary outcome

3.6.2

*Change from baseline score of the Sunnybrook grading scale at week 4.* The Sunnybrook grading scale includes three subscales: the resting symmetry subscale, the symmetry of voluntary movement subscale, and the synkinesis subscale (39). Poorer function is indicated by a higher score in the resting symmetry subscale and the synkinesis subscale, and a lower score in the symmetry of voluntary movement subscale. The final score is calculated by subtracting the total resting symmetry score and total synkinesis score from the total voluntary movement score. In this trial, the change from baseline score of each subscale and the composite score will be calculated at week 4.

*Change from baseline value of the amplitude the CMAP of the affected side at week 4.* In the ENoG test, CMAP is the summated action potentials of the stimulated motor endplates following electrical stimulation to the facial nerve. In this trial, the ENoG test will be performed, and the change from baseline value of the amplitude of the CMAP of the affected side will be calculated at week 4 (40).

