The recovery time of the facial nerve function varies among patients with BP. Patients with quick recovery can restore complete function within 2–3 weeks since the onset of BP, while in severe cases, patients took 6 month to achieve full recovery or were left with varying degrees of sequelae (2). Prolonged facial asymmetry symptoms was reported to have more severe impact on daily living (52). Therefore, in this pilot trial, we plan to focus on patients with BP who do not experience a quick recovery. We will recruit patients with a score of at least 15 on FNGS 2.0 at day 21 after the onset of BP, with scores of 15–24 on FNGS 2.0 corresponding to Grade IV (moderately severe dysfunction) to VI (total paralysis) on the original H-B scale. We plan to investigate the efficacy and safety of the two waveforms of EA in two severity groups categorized by an ENoG value of at least 20% or below 20%, the results of this study have the potential to guide the clinical use of EA for different degrees of severity of BP.

Our study has several limitations. First, promoting the quick recovery of facial nerve function is important for all patients with BP, however, we will only include participants who presented with moderately severe to complete paralysis at day 21 after the onset of BP. Thus, the effects of EA in cases of mild severity will not be evaluated in this study. Second, in this study, we will not include a conventional acupuncture group or sham EA group. We expect to obtain the better EA waveform for treating BP in this trial, and we plan to verify its efficacy and safety by comparing it with conventional acupuncture or sham EA in future studies. Third, though in previous study of acupuncture therapy for BP, differences of symptom improvement among different treatment groups were observed after 4-week treatment (36), however, for patients with severe facial nerve impairment, the 4-week treatment period may be relative short. Moreover, we did not establish a post-treatment follow-up period to assess the long-term effects of the treatment. In future research, it is worth to explore the effect of longer treatment period, and also the long-term effect of EA for BP. Finally, although we plan to recruit patients from three hospitals to screen more potential participants, all of these hospitals are in the same city, which may lead to poor representativeness of the participants.

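### Last observation carried forward is the only missing-data method, and on the text it imputes no change for anyone without a week-4 score; this can shrink or fabricate a waveform difference, depending on dropout

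*Protocol article*

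**What the plan says.** Section 3.9 (Statistical analysis) fixes one rule for all missing data: "Missing data will be substituted using the last observation carried forward method". It names no alternative and no sensitivity analysis. It plans t tests or Mann–Whitney tests at a two-sided 0.05 level in both intention-to-treat and per-protocol populations, followed by a power analysis that uses the effect sizes obtained.

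The outcomes share one time point. For FNGS 2.0 (section 3.6.1): "The primary outcome of this trial will be the change from baseline score of FNGS 2.0 at week 4". For Sunnybrook (section 3.6.2): "the change from baseline score of each subscale and the composite score will be calculated at week 4". For ENoG (section 3.6.2): "the change from baseline value of the amplitude of the CMAP of the affected side will be calculated at week 4". No efficacy assessment between baseline and week 4 is described, and the Discussion adds: "we did not establish a post-treatment follow-up period".

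On natural history, the Introduction reports "most patients experiencing important improvement within 3 weeks" and says that without treatment "approximately 70% of patients achieve complete recovery within 6 months".

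**The concern.** Carrying the last value forward assumes that a patient stays where last seen. With baseline and week 4 as the only described assessments, the last value before a missing week-4 score is the baseline score, so the imputed change is exactly 0. In a condition that tends to improve, and with active treatment in both arms, that is a poor default. The imputed values are then analysed as if they had been observed.

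The waveform comparison is at stake. The arm that loses more participants looks worse for that reason alone, and a real difference is diluted even when losses are balanced. At 30 per arm within a severity level, three missing participants are 10% of an arm. The sponsor intends to carry the better waveform into later trials, and the obtained effect sizes go straight into the planned power analysis, so any distortion is passed on.

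**Working it through.** **Inputs from the protocol article.** There are 60 participants per severity level and 1:1 allocation (section 3.8), so 60 / 2 = 30 per arm in each level. The test level is 0.05, two-sided (section 3.9). The plan gives no dropout rate, mean change, SD or power, so it has no figure of its own to reproduce.

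**Assumptions.** Improvement is the fall in FNGS 2.0 score. Mean improvement μ is 2, 4 or 8 points, and SD σ is 4 (range 3 to 5 where stated). Dropout m is unrelated to outcome, there is no interim score, and the test is the t test.

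**Step 1: mean.** A share m of the arm is set to 0, so the arm mean becomes (1 − m)μ. The expected difference between arms is (1 − mA)μA − (1 − mB)μB.
- Equal dropout: the true difference is multiplied by (1 − m). At 10% the factor is 0.90, so 0.50 SD becomes 0.45 SD.
- Unequal dropout, no true difference: the false difference is μ × (mB − mA). At 5% versus 15% it is 0.10 × μ = 0.2, 0.4 and 0.8 points for μ = 2, 4 and 8. At 5% versus 20% it is 0.15 × μ = 0.3, 0.6 and 1.2 points.
- Equal dropout, no true difference: the false difference is 0.

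**Step 2: SD.** The SD after imputation is σ × √[(1 − m)(1 + m(μ/σ)²)]. At m = 0.10:
- μ = 4, σ = 5: √(0.9 × 1.064) = 0.98
- μ = 4, σ = 4: √(0.9 × 1.1) = 0.995
- μ = 8, σ = 3: √(0.9 × 1.711) = 1.24

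For μ of 4 to 8 and σ of 3 to 5, the SD factor is thus 0.98 to 1.24. The standardized effect is multiplied by 0.90 divided by that factor, which is 0.92 down to 0.73.

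**Step 3: error rates.** Simulation with 40,000 trials, 30 per arm and σ = 4. For power, the true difference is d = 0.5 (2 points), with the poorer arm improving by μ and the better by μ + 2.

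| Mean improvement μ | Type I error, 5% vs 15% dropout | Type I error, 5% vs 20% dropout | Power, 10% dropout in both arms |
|---|---|---|---|
| 2 | 5.5% | 6.2% | 41% |
| 4 | 6.7% | 9.2% | 39% |
| 8 | 10.6% | 17.3% | 31% |

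Repeat runs differ by a few tenths of a percentage point. With 10% dropout in both arms and no true difference, type I error stays at about 5%.

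**Step 4: comparator.** Leaving out the missing participants gives 30 × 0.9 = 27 completers per arm. Power for d = 0.5 from the noncentral t distribution is then 44% (48% with all 30). Under these assumptions, filling in zeros does worse than not imputing at all.

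**The case against.** Several stronger readings are tempting, and the documents do not support them.

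- **That every participant without a week-4 score certainly gets a zero.** The measurement schedule is in Figure 2, which is not shown. An interim score would replace the zero by an understated change, and the figures above would no longer apply.
- **That the rule necessarily biases the comparison.** A false difference needs unequal dropout, and the documents give no reason to expect it. Both arms receive active electroacupuncture with the same points, needling, duration and number of sessions, and participants are blinded. The unequal rates are assumptions.
- **That no change is implausible for everyone enrolled.** The recovery statements describe Bell palsy in general. The trial takes patients still at 15 or more on FNGS 2.0 at day 21, half of them with ENoG below 20%, for whom the Introduction expects recovery to take at least 4 months. Mean change over 4 weeks may be small there, and the bias with it.
- **That the SD is badly distorted.** It may barely move. Nor does the protocol say that the pilot is meant to deliver an SD; it speaks of feasibility, safety and a preliminary basis for later work.

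The 44% for completers also assumes dropout unrelated to outcome, which is the most favourable case for them. A per-protocol analysis is planned, but it is not presented as a check on the imputation and it gives up the full randomised comparison.

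These points limit the size and certainty of the concern. They do not make the rule suitable: it is stated, it is the only one, and the direction and size of its error depend on a dropout pattern that nobody can know in advance.

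**Conclusion.** The concern holds in conditional form. On the text, the rule imputes a change of 0; with an interim assessment, it would still freeze recovery part-way. Where patients improve on average, it dilutes a true difference under equal dropout and creates a false difference, equal to mean improvement times the dropout gap, under unequal dropout.

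The consequences run from negligible at 2 points of improvement to material at 8 points, which is the top of the assumed range and should not be read as the expected case. The effect is probably smallest in the ENoG below 20% level. All sizes rest on assumed mean change, SD and dropout, on no interim score, and on dropout unrelated to outcome.

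For a pilot this should be fixed before analysis; it does not invalidate the design.

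**What to change.** Replace the last-observation rule in the primary intention-to-treat analysis by one of two approaches:

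- a baseline-adjusted model of all observed week-4 scores, valid if data are missing at random given arm, severity level, centre and baseline; or
- multiple imputation from the same variables, carried out by arm.

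Add one delta-adjusted sensitivity analysis, in which unobserved week-4 scores are shifted away from the missing-at-random prediction. Keep last observation carried forward at most as a labelled sensitivity analysis. Report the amount of missing data by arm and severity level, and state whether any efficacy score is taken between baseline and week 4.

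It would also help to seek the week-4 FNGS 2.0 score from participants who stop sessions early.

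Cost: a paragraph of analysis text and a little more programming, with no extra participants. Obtaining week-4 scores after early stopping is a small additional data-collection effort in a trial that is already running.

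### The planned power analysis uses the obtained effect sizes, so it largely restates the p-value and cannot evaluate the power of the study

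*Protocol article*

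**What the plan says.** Section 3.9 of the protocol article (Statistical analysis) states: "After the primary statistical analysis, a power analysis will be conducted using G*Power software version 3.1.9.7". Its purpose is "to evaluate the statistical power of the study given the sample sizes and the obtained effect sizes". On testing, the same section says "All statistical tests will be two-sided, with the significance level set at 0.05", and that Student's t "test or Mann–Whitney U test will be used for comparisons of numerical variables".

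Section 3.8 (Sample size) notes that "studies with comparable designs are lacking" and takes the size from a cited rule for pilot trials: "a pilot trial of at least 55 participants would minimize the overall sample size for small to medium standardized effect sizes". It concludes that "we will recruit 120 participants in total, with 60 participants at each severity level" and that "participants will be assigned to the two treatment groups in a 1:1 ratio". It gives no target difference, standard deviation or target power.

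The Discussion (section 4) expects the trial to identify the better waveform. That waveform is then to be tested against conventional acupuncture or sham electroacupuncture.

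**The concern.** The power of a study is a property of its design at a stated true effect. Putting the observed effect in place of the true one gives a number that the test result has already fixed. The step is presented as an evaluation of the study, but for the t test it adds nothing to the p-value.

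What is at stake is interpretation. No target effect or power was set in advance, so this figure would be the only statement about power that a reader gets. After a non-significant comparison it will always look low, even if the data already exclude a worthwhile difference. After a large chance effect it will look high and lend unearned support to the choice of waveform.

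**Working it through.** **Inputs from the documents.** Two-sided α = 0.05 and t test or Mann–Whitney (section 3.9). 60 per severity level, 1:1, so n = 60/2 = 30 per arm within a level (section 3.8). Pooling both levels would give 60 per arm.

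**The plan's own figure.** The only stated figure is the total: 2 × 60 = 120, and 60 meets the quoted minimum of 55. No power calculation is stated, so there is none to reproduce.

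**Step 1: observed power as a function of p (t test).** Degrees of freedom are 2n − 2. A given p fixes |t|, then the obtained d = |t| × √(2/n). Observed power is the probability that a noncentral t with noncentrality d × √(n/2), which equals |t|, falls outside ± the critical value.

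Example, n = 30, p = 0.10: |t| = 1.672 on 58 df; d = 1.672 × √(2/30) = 0.432; critical value 2.002; power 38%.

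| p | obtained d, 30 per arm | observed power, 30 per arm | observed power, 60 per arm |
|---|---|---|---|
| 0.001 | 0.895 | 93% | 92% |
| 0.01 | 0.688 | 75% | 74% |
| 0.05 | 0.517 | 50% | 50% |
| 0.10 | 0.432 | 38% | 38% |
| 0.20 | 0.335 | 25% | 25% |
| 0.50 | 0.175 | 10% | 10% |

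Once p is known, doubling the sample moves the answer by about a point at most. With 30 per arm, no non-significant result can exceed 50.3%.

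**Step 2: how well it estimates true power.** Assume a true d of 0.5; the protocol gives no value, so this is illustrative. True power with 30 per arm is 48%. The central 95% of obtained d then runs from about 0 to 1.04. Observed power is 5% at d = 0 and 98% at d = 1.04. In 100,000 simulated trials the 5th and 95th percentiles of observed power were 7% and 95%. For other assumed true values the same percentiles were:

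- d = 0.2 (true power 12%): 5% to 68%
- d = 0.35 (true power 27%): 5% to 86%
- d = 0.8 (true power 86%): 30% to nearly 100%

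**Step 3: what an interval would say instead.** With standard error √(2/30 + d²/120), the approximate 95% interval for the standardized difference is d ± 1.96 × SE.

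- Obtained d = 0: SE = 0.258, interval −0.51 to 0.51, observed power 5%.
- Obtained d = 0.5: SE = √(0.0667 + 0.0021) = 0.262, interval −0.01 to 1.01, observed power 48%.

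Both results are non-significant. The first has the lowest observed power possible, yet it excludes differences beyond about half a standard deviation in either direction. The second has higher observed power and leaves a difference of one standard deviation open. Observed power thus ranks the two results the wrong way round as evidence against a large difference.

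**Step 4: power that does describe the design.** At pre-set effects with 30 per arm, power is 12% at d = 0.2, 48% at d = 0.5 and 86% at d = 0.8. These figures can be stated before any data are seen.

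**The case against.** The strongest defence is that the step follows the primary analysis and leaves the estimate, test, type I error and analysis populations untouched. No passage sets a power threshold or says that a null will be called underpowered. This stands and limits the severity. It does not make the figure informative.

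The fixed link with p is exact only for the t test. Under Mann–Whitney, power computed from a standardized effect follows p closely but not exactly. This also stands, and the practical conclusion is the same.

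A reader might infer that the obtained effect will size the next trial. The documents do not say so. The stated purpose concerns this study only, the introduction speaks generally of a basis for later research, and the next study described in the Discussion has a different contrast. The pilot-size rationale makes such use plausible, but it remains a risk.

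A reader might also infer that the cited pilot rule requires a particular sizing method, which this step defeats. Section 3.8 reports only the minimum number and its aim, so nothing further can be built on it. Nor is it right that the plan omits the standard deviation: section 3.9 presents normally distributed data as mean and standard deviation. That a condensed article does not mention confidence intervals is not itself a fault.

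**Conclusion.** The point holds as a fault in a stated analysis: the calculation cannot do what section 3.9 says it is for. With 30 per arm, every non-significant t test returns about 50% or less. At an assumed true d of 0.5 the reported figure could lie anywhere from about 5% to 98%, against a true power of 48%.

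The p-to-power figures need only the t test, α = 0.05 and equal arms of 30 or 60. The spread in step 2 also rests on normal data with equal variances and on the assumed true effects.

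The consequence is a possible misreading of the pilot, which matters because it is expected to choose a waveform and gives no other power statement. The severity is moderate: the correction is worth making, but the primary comparison is sound without it.

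**What to change.** Delete the sentence on the G*Power analysis in section 3.9. In its place, state that for each severity level the between-waveform difference in the primary outcome (change in FNGS 2.0 at week 4) will be reported with its 95% confidence interval, and that precision will be judged from that interval.

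If a power statement is wanted, give it at effect sizes fixed in advance and independent of the results. The values in step 4 are illustrations; the investigators should choose and justify their own.

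The cost is one sentence, with no new data and no change to enrolment or to the primary test. It is best made before results are seen. If they are already known, leave observed power out of the report and give the interval.
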